## Design

BGDP is a two-armed cluster randomised control trial in 18 secondary schools. The trial includes process, economic, quantitative and qualitative evaluations. The 18 schools will be recruited from state secondary schools (excluding Special Educational Needs, dance academies and privately/independently funded schools) operating within three Local Authorities: Bristol City Council, North Somerset Council, and Bath and North East Somerset Council. We aim to recruit up to 33 Year 7 girls from each school, with a minimum of 25 participants in each (450–594 participants overall). Schools must have at least 30 Year 7 girls, and be able and willing to allocate space for two after-school sessions per week for 20 weeks.

All schools fulfilling the inclusion criteria will be invited to participate and the first 18 schools that agree to participate will be enrolled. Additional schools will be placed in a reserve pool. If fewer than 25 girls are recruited in a given school, we will recruit a different school. Nine schools will be randomly assigned to the intervention arm and nine to the control arm.

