### Sample size

Sample size calculations were performed to detect a mean difference of ten minutes of weekday MVPA between the intervention and control groups. The un-inflated sample size required for analysis to detect a difference of 10 minutes/day MVPA - assuming a standard deviation of 18 minutes [14] with 90% power and 5% two-sided alpha is 68 per arm. We estimated the 95% Confidence Interval (CI) for the school-associated Intra-class Correlation (ICC) in the pilot study to be < 0.001 to 0.087. If we assume that 20% of participants will not provide primary outcome data, the mean cluster size for analysis will be 24, resulting in a design effect of 3.0 using the upper 95% confidence limit for ICC. Thus, we will recruit a total of 18 schools and at least 450 girls.

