### Economic analyses

Economic analysis will be set within a cost 'effectiveness’ framework. The mean incremental costs associated with intervention delivery at the school level will be estimated from a public sector perspective [14]. Public sector costs will be related to incremental change in accelerometer-derived MVPA minutes per weekday and incremental change in EQ-5D-Y scores to estimate cost per minute of MVPA, cost per Quality-adjusted Life Year (QALY), average cost per school and average cost per user, with the associated CIs reported. EQ-5D-Y will be administered at T0, T1 and T2. We will also extend the balance sheet framework to include the proportion of participants meeting the 60-minute per day MVPA recommendation. Programme costs will also be determined at the school level.

Confidence intervals for the *incremental cost-effectiveness ratio* (ICER) will be calculated using bootstrapping at the school level. If appropriate we will produce cost-effectiveness acceptability curves for a range of thresholds and conduct threshold analysis to compare our cost per QALY estimates with National Institute for Health and Care Excellence (NICE) benchmark values. The time frame for the health economic evaluation is the length of the study, as the focus is to consolidate learning from our feasibility study in a full trial, and not to attempt to make long term predictions of cost-effectiveness at this stage. Uncertainty will be explored using sensitivity analyses and findings will be presented for a range of decision makers at the societal and funder levels, including Local Authorities and the National Health Service (NHS), from a public sector perspective.

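### A plain school-level bootstrap with nine schools per arm makes economic intervals on the effect and net-benefit scale somewhat too narrow; a small-sample form should be named

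*Protocol article*

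**What the plan says.** In the protocol article, Economic analyses, ICER intervals "will be calculated using bootstrapping at the school level". The Design section fixes the number of units: "Nine schools will be randomly assigned to the intervention arm and nine to the control arm".

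The Economic analyses section also promises "average cost per school and average cost per user, with the associated CIs reported", without saying how the cost intervals are to be formed. It adds, conditionally, "If appropriate we will produce cost-effectiveness acceptability curves for a range of thresholds", together with a comparison of cost per QALY against NICE benchmark values.

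The section does not name an interval type (percentile, BCa, bootstrap-t), does not say whether girls are resampled within schools, and mentions no correction for a small number of schools. It makes no claim about coverage.

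**The concern.** Schools are randomised, so resampling whole schools respects the clustering. The difficulty is the number of them. A bootstrap of k units treats the observed k as the whole population, so its variance uses divisor k instead of k − 1, and percentile limits behave like normal limits instead of t limits. With k in the hundreds neither matters. With k = 9 per arm both do, and both shorten the interval.

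At stake is how certain the economic results look to Local Authorities and the NHS. Intervals for the incremental effect and net benefit would be too short. An acceptability curve is simply the share of draws with positive net benefit, so it would inherit the same overconfidence. The primary effectiveness analysis, a mixed-effects regression, is not touched.

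**Working it through.** **Inputs from the article.** Nine schools per arm (Design). From Sample size: a target of 10 minutes; SD 18, 90% power, 5% two-sided alpha and 68 per arm ("assuming a standard deviation of 18 minutes [14] with 90% power and 5% two-sided alpha is 68 per arm"); pilot ICC interval ("Intra-class Correlation (ICC) in the pilot study to be < 0.001 to 0.087"); 24 girls per school and a design effect of 3.0.

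**The article's own figures reproduce.**
- n per arm = 2 × (1.960 + 1.282)² × 18² / 10² = 68.1, against 68 stated.
- Design effect = 1 + 23 × 0.087 = 3.00.
- 68 × 3.00 = 204 per arm; 204 / 24 = 8.5, so nine schools per arm and 18 in all.

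**Standard error of the one-stage bootstrap.** Drawing nine of nine within arm gives SE ratio = sqrt((k − 1)/k) = sqrt(8/9) = 0.943, about 6% too small. This needs no assumption about costs, ICC or distribution. The simulated ratio was also 0.943.

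**Coverage for a difference or net benefit.** Percentile limits act like ±1.960 × 0.943 = ±1.848 true-scale standard errors, where t on 16 df needs 2.120.
- Approximate coverage: P(|t16| < 1.848) = 91.7%.
- Simulated, arm difference (20,000 trials): 91.3%. Resampling all 18 schools without regard to arm: 91.7%.
- Simulated, net benefit (5,000 trials per setting, ICC 0.001 to 0.087): 91.0–92.0%.
- Width relative to the t interval: 0.943 × 1.960 / 2.120 = 0.87.

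**Acceptability curve, by example.** A net-benefit t statistic of 1.746 corresponds to probability 0.95 on 16 df. The draws would show it as 1.746 / 0.943 = 1.85 normal deviates, or about 0.97.

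**The ICER itself.** What matters is how far the effect lies from zero in standard errors. The SD of a school mean is sqrt(18² × ICC + 18² × (1 − ICC)/24), which is 3.72 at ICC 0.001 and 6.36 at 0.087. Multiplying by sqrt(2/9) gives SEs of the arm difference of 1.75 and 3.00 minutes. The simulations assumed a cost of 8,000 per intervention school, between-school CV 0.05–0.5 and no control cost.

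| Effect, ICC | Effect / SE | Draws with effect ≤ 0 | ICER percentile coverage |
|---|---|---|---|
| 10 min, 0.001 | 5.7 | 0.0% | 91–92% |
| 10 min, 0.087 | 3.3 | 0.8% | 94–95% |
| 5 min, 0.001 | 2.9 | 1.8% | 95% |
| 5 min, 0.087 | 1.7 | 11% | 95–96% |

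At 10 minutes, coverage rises from 92.9% at ICC 0.04 to 93.6% at 0.06. A second set of simulations gave 90–93% for 10 minutes with low ICC, and 95–96% at ICC 0.087 or 5 minutes. BCa limits for the ICER are no safe substitute: at 5 minutes they cover 94% at ICC 0.001 but 85% at 0.087.

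**Other bootstrap forms.** Bootstrap-t on net benefit covers 95.0–95.5%. The t(16) interval on school means covers 94.3–95.5%. Multiplying the bootstrap SE of a difference in school means by sqrt(9/8) recovers that interval's SE. A two-stage bootstrap (schools, then girls) errs the other way: SE ratio 1.09–1.35, coverage 95.5–99.3%.

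**Average cost per school, only if bootstrapped in the same way.** Nine intervention schools alone give width ratio 0.943 × 1.960 / 2.306 = 0.80 and coverage of about 89–90%.

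**The case against.** The strongest reply is that the article fixes only the resampling unit, and fixes it correctly. The type of interval and any finite-sample correction are details that a journal article commonly leaves to a fuller plan, and the choice left open decides the result: a bootstrap-t is near nominal and a two-stage scheme is conservative. This stands to the extent that the 91–92% figure must be tied to the one-stage percentile form. It does not remove the point, because that form is the ordinary reading of a school-level bootstrap, and nine schools per arm is fixed.

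The second reply is that the sentence concerns the ICER, and that coverage simulated for a difference in minutes says little about a ratio. This also stands. A reader might infer that every cost-effectiveness interval in the trial will cover about 91%. The calculations do not support that: at the ICC on which the article bases its design effect, the percentile ICER interval covers close to 95%. That is no endorsement of the ratio interval. Its coverage rises because draws with an effect near or below zero stretch it into values that have no useful meaning as a cost per minute gained.

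A reader might also infer an inflated false-positive rate, but the article plans no hypothesis test on the economic results. Nor does it say that the cost-per-school interval will be bootstrapped. Finally, cost-effectiveness is a secondary aim, acceptability curves are conditional, and sensitivity analyses are planned; all of this limits the consequence.

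**Conclusion.** The point holds in a limited form. With nine schools per arm, the plain one-stage school bootstrap understates the standard error by about 6%. Percentile 95% intervals for the incremental effect and net benefit then cover about 91–92% and are about 13% too narrow, and acceptability probabilities from the same draws are too extreme. For the ICER, percentile coverage ranges from about 90–93% (10-minute effect, low ICC) to about 94–96% (ICC 0.087, or a 5-minute effect), and in the latter settings the interval is hard to interpret.

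The factor sqrt(8/9) follows from the design alone. The coverage figures rest on the one-stage percentile form, which the article does not name, and on normal school means and equal cluster sizes. The ICER and net-benefit figures also rest on the assumed costs. The shortfall is modest and comes from the small number of schools, not from the choice of school as the unit; resampling girls alone would ignore the clustering. It is worth correcting because its direction is known in advance and the remedy is cheap.

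**What to change.** Keep the school as the resampling unit, within arm, and add a sentence to Economic analyses that names a small-sample method. Report uncertainty on the incremental-effect and net-benefit scale by either:

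- a bootstrap-t; or
- estimate ± t(16 df) × bootstrap SE × sqrt(9/8).

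Both restore about 95% coverage in the simulations. The 16 df assume unadjusted school means and should be reconsidered if the economic model adjusts for covariates. Build any acceptability curve from the same corrected net-benefit distribution, not from the raw draws. State how the ICER will be presented when draws have an effect near or below zero. If average cost per school is bootstrapped too, apply the same correction with t on 8 df.

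The cost is a small code change and limits about 15% wider (2.120 / (1.960 × 0.943) = 1.147). Recruitment, data collection and the primary analysis are unaffected.

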### End of study qualitative assessment

Qualitative methods will be used at the end of the intervention to ascertain elements of the intervention that worked well, potential improvements, and factors that might affect future dissemination/roll-out.

A focus group will be conducted with a selection of participants at all nine intervention schools. Participants will be purposively sampled to represent a range of attendance levels, with approximately 6–8 participants per group. The focus groups will address facilitators, barriers to participants’ engagement, perceived impact and their views on promoting the dance project for a larger roll-out.

Semi-structured telephone interviews will be conducted with all dance instructors, addressing their experiences of delivering the intervention, barriers and facilitators, and factors central to supporting their continued involvement if the programme was implemented more widely. Semi-structured interviews will also be conducted with the primary contact at each intervention school, focusing on the logistical and organisational factors affecting delivery within school and how best to market the project for wider implementation. Interviews and focus group recordings will be transcribed verbatim and analysed via NVivo software, using thematic analysis [33].

### Current status of trial (23/09/2013)

18 schools have been recruited, with four reserves. Dance instructors have been recruited to deliver the taster and after-school dance sessions. Baseline data is currently being collected. Randomisation of schools to control and intervention arms will be conducted in October 2013, and schools will be informed of their arm allocation soon after. The after-school dance sessions will be delivered between January and June/July 2014 in the nine intervention schools.

## Discussion

This paper describes the rationale and methods that will be used for the BGDP cluster randomised controlled trial. The trial is attempting to increase levels of PA amongst Year 7 girls in the greater Bristol area, UK.

## Abbreviations

BMI: Body mass index; CI: Confidence interval; CONSORT: Consolidated standards of reporting trials; EQ-5D-Y: EuroQol 5D youth survey; ICC: Intra-class correlation; ICER: Incremental cost-effectiveness ratio; ITT: Intention-to-treat; MVPA: Moderate to vigorous physical activity; NHS: National Health Service; NICE: National Institute for Health and Care Excellence; PA: Physical activity; QALY: Quality adjusted life year; SDT: Self-determination theory.
